# A community-based cluster randomised controlled trial to evaluate the effectiveness of different bundles of nutrition-specific interventions in improving mean length-for-age z score among children at 24 months of age in rural Bangladesh: study protocol

**DOI:** 10.1186/s12889-017-4281-0

**Published:** 2017-05-02

**Keywords:** Randomised controlled trial, Bundling, Nutrition interventions, Stunting, Length-for-age, First 1000 days of life

## Abstract

**Background:**

Prevalence of stunting among under-five children in Bangladesh is 36%, varying with geographic and socio-economic characteristics. Previously, research groups statistically modelled the effect of 10 individual nutrition-specific interventions targeting the critical first 1000 days of life from conception, on lives saved and costs incurred in countries with the highest burden of stunted children. However, primary research on the combined effects of these interventions is limited. Our study directly addresses this gap by examining the effect of combinations of 5 *preventive* interventions on length-for-age z-scores (LAZ) among 2-years old children.

**Methods:**

This community-based cluster randomised trial (c-RCT) compares 4 intervention combinations against one comparison arm. Intervention combinations are: 1) Behaviour change communication (BCC) on maternal nutrition during pregnancy, exclusive breastfeeding, and complementary feeding, along with prenatal nutritional supplement (PNS) and complementary food supplement (CFS); 2) BCC with PNS; 3) BCC with CFS; and 4) BCC alone. The comparison arm receives only routine health and nutrition services. From a rural district, 125 clusters were selected and randomly assigned to any one of the five study arms by block randomisation. A bespoke automated tab-based system was developed linking data collection, intervention delivery and project supervision. Total sample size is 1500 pregnant women, with minimum 1050 resultant children expected to be retained, powered to detect a difference of at least 0.4 in the mean LAZ score of children at 24 months, the main outcome variable, between the comparison arm and each intervention arm. Length and other anthropometric measurements, nutritional intake and other relevant data on mother and children are being collected during enrolment, twice during pregnancy, postpartum monthly till 6 months, and every third month thereafter till 24 months.

**Discussion:**

This c-RCT explores the effectiveness of bundles of *preventive* nutrition intervention approaches addressing the critical window of opportunity to mitigate childhood stunting. The results will provide robust evidence as to which bundle(s) can have significant effect on linear growth of children. Our study also will have policy-level implications for prioritising intervention(s) tackling stunting.

**Trial registration:**

The study was retrospectively registered on May 2, 2016 and is available online at ClinicalTrials.gov (ID: NCT02768181).

**Electronic supplementary material:**

The online version of this article (doi:10.1186/s12889-017-4281-0) contains supplementary material, which is available to authorized users.

## Background

Globally in 2013, 161 million children under the age of five years (U-5 children) had a height-for-age Z score more than 2 standard deviations (SD) below the median of WHO Multicentre Growth Reference Study (MGRS) Child Growth Standard (termed ‘stunting’), and half of these children resided in Asia [1]. Although the stunting prevalence is decreasing worldwide, reductions in South Asia have been slower (36% since 1990) compared to 57% reduction in Europe and more than 70% in East Asia and the Pacific [2]. Stunted children have higher mortality [3], lower academic attainments [4], short stature as adults [5], reduced economic productivity [6], reduced cognition [7] and have a higher risk of cardio-metabolic diseases in adulthood [8], all contributing to the ‘stunting syndrome’ [9], and the trans-generational cycle of undernutrition and poverty [10]. Thus, stunting is a major public health problem in South Asia. In Bangladesh, the latest Demographic and Health Survey (2014) [11] reports that stunting prevalence has decreased to 36.1%. Despite a reduction in the past decade [12], national stunting prevalence remains high [13], with higher levels in rural areas (37.9%) and among the poorest populations (50.2%). Trends also show widespread geographic disparity - stunting has declined by about 2–3 percentage point per year in most regions except no change in *Sylhet* division, the north-eastern region [11].

### Global goals related to stunting

Although unaddressed by the Millennium Development Goals, reduction of stunting prevalence became the focus of several high-profile nutrition initiatives such as Scaling Up Nutrition (SUN, 2010) [14], World Health Assembly 2012 [15] and Nutrition for Growth 2013 [16]. The World Health Assembly 2012 has a target of 40% reduction of U-5 stunting by 2025. Hence, the recent Sustainable Development Goals (SDGs) adopted by the UN in 2015 included stunting reduction as one of their goals (SDG 2.2) [17].

### The critical window of opportunity

Childhood stunting is considered to have in utero origins [18]. The first 1000 days of life (conception to postpartum two years) is regarded as a critical ‘window of opportunity’ for growth and development [19]. The long-term interactions of both proximal (i.e. biological and environmental) and distal (i.e. socioeconomic) factors play significant roles during this period in influencing the linear growth of children [20]. The proximal factors of childhood stunting in South Asia include undernourished mothers, limited dietary diversity during pregnancy, poor infant and young child feeding practices (IYCF) including suboptimal breastfeeding and/or complementary feeding, and inappropriate sanitation and hygiene [21]. However, even short-term improvements in nutritional status (in utero and postnatal) can result in substantial mean height gain of the child even within a single generation [22].

### Potential interventions to tackle stunting

In the Lancet Maternal and Child Nutrition Series 2013, Bhutta et al. (2013) statistically modelled the effect of 10 nutrition-specific interventions on lives saved and economic costs in 34 countries containing the majority of the children with stunted growth [23]. They suggested that at an estimated additional cost of $9.6 billion per annum for 90% coverage of these interventions, one-fifth of stunting among the U-5 children can be averted. However, there is a need for primary research to test and clarify the combined impact of nutrition-specific interventions as packages. They agreed about this gap and that further trials are needed.

### Relevance of the present study

We have adapted five *preventive* interventions to create our own interventions bundles, based on Bhutta et al.’s list considering feasibility of scale-up in low resource settings and targeting the first 1000 days of life (from conception to two years of age). Our interventions include, a) Behaviour change communication (BCC) on nutrition and health-related practices during pregnancy; b) BCC on exclusive breastfeeding (EBF) for postnatal first 6 months; c) BCC on age-specific complementary feeding (CF) with continued breastfeeding thereafter till 23 completed months; d) Nutritional supplementation during pregnancy (PNS) with preventive doses of micronutrients, and partial provision of protein and lipids; e) Nutritional supplementation for children (CFS) during 6 to 23 completed months of age, with preventive doses of micronutrients, and partial provision of protein and lipids. In essence, this randomized controlled trial provides a crucible to see how different nutritional interventions interact when delivered in bundled packages in community settings to affect linear growth of the child from conception to two years of age compared to the comparison arm where routines practices will run unhindered.

### Study aim and hypothesis

This study aims to test the effectiveness of the intervention bundle(s) on improving length-for-age Z score (LAZ) of children at two years of age. We hypothesised that our intervention bundle(s) would cause a change of at least 0.4 in mean LAZ of children, translating to at least 30% reduction in stunting in that arm(s), compared to that in the comparison arm.

## Methods

### Study design

This cRCT evaluates the effectiveness of 4 different combinations of the selected pre- and post-natal nutrition-specific interventions for improving children’s linear growth, compared to the comparison arm with usual practices. The three types of BCC are combined into one ‘BCC’ intervention and delivered universally in all four intervention arms. Profile of the four intervention arms are – intervention arm 1: BCC with PNS and CFS; intervention arm 2: BCC with PNS; intervention arm 3: BCC with CFS; intervention arm 4: BCC alone. (Fig. 1
**)**. The cohort of the mother-child dyads will be followed-up over the intervention period of ~36 months starting from recruitment to 24 months of child’s age.

**Fig. 1 Fig1:**
[figure not shown]
CONSORT flow diagram of the study

### Study setting

The study is being conducted in the *Habiganj* district of *Sylhet* division in Bangladesh where stunting prevalence has remained stagnant over a decade [11]. Further, the prevalence of household food insecurity was highest (77%) and the prevalence of household food deficit was second highest (33%) in Sylhet [24].

### Cluster randomization and intervention allocation

We purposively selected two adjacent sub-districts (*Bahubal* and *Nabiganj*) of *Habiganj* district. These two sub-districts have a total of 20 unions (lowest administrative unit). We excluded 8 unions, 3 being in hard-to-reach areas (seasonal flooding and poor road transport system) and 5 having intensive nutrition intervention projects implemented by other non-government organisations (NGOs). The remaining 12 unions had enough population to cover the desired sample size. Each union was then divided into clusters, each cluster comprising of ~450 households or ~2000 population (average 2–3 villages). We selected five clusters or multiples of 5 clusters from each union, 125 clusters in total following the cluster exclusion criteria detailed in Table 1. We then applied block randomisation by generating random sequence of 1–5 (each number representing a specific study arm) of 25 blocks with the analytical software Stata SE 14.2. Clusters were then allocated to arms, five at a time, based on the random sequence (Fig. 2). Taking equal numbers of clusters per arm from each union will ensure neutralizing the effect of variations, if any, of background characteristics between the unions. Allocation concealment was impractical due to community-based study design and nature of BCC intervention. However, care is taken to keep the outcome assessors blinded to the interventions allocated to specific clusters. The intervention and the evaluation teams have minimal contact to minimise information bias.

**Table 1 Tab1:** Inclusion and exclusion criteria

Exclusion criteria for clusters	
• Similar nutrition interventions currently being implemented by either government or non-government agencies in the selected cluster • The cluster is too hard to reach • The cluster includes tea gardens. Communities in tea gardens comprise of unique ethnicity, culture and lifestyle for which our intervention is not customized.	
Inclusion criteria for participants	
• All newly identified pregnant women aged 15 to 49 years • Gestational age ≤ 125 days • Permanent residents of the study area.	
Exclusion criteria for participants	
• Woman could not recall last menstrual period (LMP). • Woman not a permanent resident of the study area

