Several assumptions were considered for the sample size calculation [26]. The first assumption was that mean LAZ (our primary outcome variable) for 18–23 months old children in the comparison arm will be −2.0, and standard deviation of mean LAZ in both intervention and comparison arms will be 1, based on the mean HAZ reported in this age group in the BDHS 2011. These BDHS 2011 [25] parameters were the latest available during this protocol development. The estimates were still valid in 2015 since the latest BDHS (2014) showed similar stunting rates in *Sylhet* division [11]. Second, a 0.4 difference in mean LAZ score was expected in intervention arms compared to comparison. As the third assumption, we considered an 80% power and 5% alpha; the inter-cluster correlation coefficient of 0.06, derived from the design effect for HAZ in BDHS 2011, was used for adjustment of clustering effects. Fourth, the ratio between 4 intervention and 1 comparison arms was set at 1:1:1:1:1. Taking all the above assumptions into account, the Stata SE 13 software calculated the sample size to be 175 children per arm, which can be yielded from 25 clusters. However, to examine the secondary outcome variables between the comparison arm and individual intervention arm with a higher statistical power, the sample size in the comparison arm was doubled, thus the ratio between participant numbers in each intervention arm and comparison arm was raised to 1:2, respectively. The final allocation ratio of study participants was thus 1:1:1:1:2 for intervention arm 1: intervention arm 2: intervention arm 3: intervention arm 4: comparison arm 5. Thus, the final sample size was 175 children in each intervention arm and 350 children in the comparison arm. Considering the characteristics of the intervention, however, enrolment was during pregnancy. We therefore considered the following losses- 11% pregnancy loss due to abortion and still births (personal communication from Health and Demographic Surveillance System run by icddr,b at Mirzapur, Tangail), a 4% mortality in the first two years of life [25], 15% losses due to non-consent to participate by eligible women and loss-to-follow up. Loss-to-follow up includes refusal and migration out of study area. Thus, final sample size considering participant recruitment during pregnancy was 250 pregnant women in each intervention arm and 500 pregnant women in the comparison arm which is expected to yield the required number of children at 24 months from the enrolled cohort.

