### Statistical analysis plan

Data analysis to detect change of the primary outcome (mean LAZ) will be conducted with length measured at 1, 3, 6, 9, 12, 15, 18, 21 and 24 months of age using t-tests assuming LAZ will satisfy the normality assumption. Longitudinal assessment of significance using lag time of stunting (mean length > −2SD below median of WHO reference population) will be done by the log rank test, followed by fitting a Cox proportional hazards model for each intervention arm to determine the change in risk of stunting compared to the comparison arm. Multiple linear regression will be employed to quantify the effect of intervention in each intervention arm compared to the comparison arm in terms of mean LAZ change and some secondary continuous outcome measures including changes in mother’s weight, birth weight, diarrhoea morbidity. Logistic regression will be used on binary outcome variables which comprise most of our secondary outcomes measures (e.g. – EBF and breastfeeding initiation within 1 h of birth). All these models will be controlled for possible confounders (household food security, educational background and SES) if randomisation of the clusters does not control for differences in these factors at baseline. For regression models, we shall consider random effects of clustering. All analysis will be intention-to-treat. Quantitative data analysis will be done using Stata SE 14.2 (StataCorp LP, College Station, Texas, USA).

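### The analysis names no union or block term to match the blocked randomisation, so the standard errors of the cluster random-effects regressions get no credit for the balance if unions differ

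*Protocol article*

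**What the plan says.** **Design** (Protocol article, Cluster randomization and intervention allocation). Twelve unions remained after exclusions. "We selected five clusters or multiples of 5 clusters from each union, 125 clusters in total". The authors continue: "We then applied block randomisation by generating random sequence of 1–5 (each number representing a specific study arm) of 25 blocks", and "Clusters were then allocated to arms, five at a time, based on the random sequence". The stated reason is that "Taking equal numbers of clusters per arm from each union will ensure neutralizing the effect of variations" between unions. Every arm therefore has the same number of clusters in every union.

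**Analysis** (Protocol article, Statistical analysis plan). Mean LAZ is tested "using t-tests assuming LAZ will satisfy the normality assumption", with no cluster term mentioned. Linear, logistic and Cox models follow. On clustering the section says: "For regression models, we shall consider random effects of clustering". The level or levels of the random effect are not given. The models are to be "controlled for possible confounders (household food security, educational background and SES) if randomisation of the clusters does not control for differences" at baseline. Neither union nor block is named as a model term.

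**The concern.** When randomisation is balanced within strata, differences between strata cancel from the arm comparison. A model with a cluster random effect but no stratum term does not know this. It estimates one between-cluster variance that includes the union differences and puts all of it into the standard error of the arm effect. The interval is then wider than the design warrants and the test is conservative.

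The covariate rule does not repair this. It brings in a covariate only when randomisation has failed to balance it. Union is not on the list. Even if it were, it is balanced by construction, so an imbalance trigger would never select it. For a stratification factor, balance is the reason to include the term.

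Precision is at stake in the regression estimates of mean LAZ and of the secondary outcomes. The Sample size section doubled the comparison arm to gain power for those secondary comparisons.

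**Working it through.** **Inputs** (Protocol article, Sample size): SD 1; ICC 0.06; 25 clusters per arm; 175 children per intervention arm (7 per cluster) and 350 in the comparison arm (14 per cluster); effect 0.4 ("a 0.4 difference in mean LAZ score was expected in intervention arms compared to comparison"); alpha 5%, taken as two-sided. **Assumption:** f is the share of between-cluster variance lying between unions or blocks. The documents give no value, so f = 0, 0.25, 0.50 and 0.75 are shown.

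**The plan's own figure.** At 80% power, n per arm before clustering is 2 × (1.96 + 0.84)² / 0.4² ≈ 98.1. With 7 children per cluster the design effect is 1 + 6 × 0.06 = 1.36, and 98.1 × 1.36 ≈ 134, not 175. At 175 v 175 the power is 89.4%. This mismatch is a separate matter. Below, 175 and 350 are taken as given. The enrolment step does reproduce: 250 × (1 − 0.30) = 175.

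**Variance of an arm difference, 175 v 350.**
- Reported by a cluster random-effects model without union: 0.94/175 + 0.94/350 + 2 × 0.06/25 = 0.00537 + 0.00269 + 0.00480 = 0.01286, so SE 0.1134. This does not depend on f.
- True, given the balance: 0.94/175 + 0.94/350 + 2 × (1 − f) × 0.06/25.
- Child-level t-test: 1/175 + 1/350 = 0.00857, so SE 0.0926.

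**Consequences for the random-effects regression.** Actual size = 2 × [1 − Φ(1.96 × 0.1134 / SE_true)]. Power without the term = Φ[(0.4 − 1.96 × 0.1134) / SE_true]. Power with it = Φ(0.4 / SE_true − 1.96).

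| f | True variance | True SE | SE could fall by | Actual size, no stratum term | Power without / with |
|---|---|---|---|---|---|
| 0 | 0.01286 | 0.1134 | 0% | 5.0% | 94.2 / 94.2% |
| 0.25 | 0.01166 | 0.1080 | 5% | 4.0% | 95.0 / 95.9% |
| 0.50 | 0.01046 | 0.1023 | 10% | 3.0% | 95.9 / 97.5% |
| 0.75 | 0.00926 | 0.0962 | 15% | 2.1% | 96.8 / 98.6% |

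**The t-test.** Its SE of 0.0926 is below the true SE in every row. Its actual size is about 11.0%, 9.3%, 7.6% and 5.9% for f = 0, 0.25, 0.50 and 0.75. It would become too large only where 0.00806 + 0.0048 × (1 − f) < 0.00857, that is, f above about 0.89.

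**Simulation check** (4000 runs, 25 clusters per arm, 7 children per cluster in both arms, 12 unions, f = 0.5). With a true effect of 0.4, the mean estimate was 0.4025 and its empirical SE 0.115, with or without union in the model. With no effect, rejection was 3.3% without union, 4.8% with union and 7.1% for the child-level t-test. The estimate is unchanged and only its stated uncertainty differs.

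**Degrees of freedom at cluster level.** No stratum: 125 − 1 − 4 = 120. Union: 125 − 12 − 4 = 109. Block: 125 − 25 − 4 = 96.

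**The case against.** Four points can be made on the other side.

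1. *The benefit of the balance is not lost.* A reader might infer that leaving out union undoes the neutralising of union differences. It does not. Equal clusters per arm in each union remove union differences from the estimate however it is modelled. This stands, and only the credit in the standard error is missing.
2. *Standard errors are not too large throughout.* A reader might infer that the whole analysis, including the primary test, errs on the safe side. The documents do not support that. The t-tests named for LAZ carry no stated cluster term and, read as child-level tests, are anti-conservative at every share considered. This stands and confines the point to the random-effects regressions.
3. *Silence in a condensed article.* The level of the random effect is not stated, so a union level is not excluded, and stratum terms are often left to a statistical analysis plan that is not shown here. This stands in part: one cannot say that the trial will omit union. But the article does fix a covariate rule, and as worded that rule cannot bring in a factor balanced by design.
4. *The union variance is unknown and may be small.* The allocation section allows that there may be no union differences, and the Discussion expects little variation between clusters. At f = 0 the effect is nil, and nothing in the document supports a share as high as 50% or 75%. This stands and lowers the weight of the point.

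**Conclusion.** The point holds as a minor efficiency improvement. The randomisation is balanced within unions, the stated analysis names no matching term, and its covariate rule would not add one. For the cluster random-effects regressions at 175 v 350 children, the avoidable excess runs from nothing (no union differences) to a standard error that could be about 15% smaller (75% of cluster variance between unions or blocks). The size of the nominal 5% test falls correspondingly from 5.0% to 2.1%. Power stays above 94% throughout and the loss is under 2 points.

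These figures rest on the plan's ICC of 0.06 and SD of 1, on the planned numbers at 24 months, and on an assumed range for f. The conclusion covers neither bias in the point estimate, which the design prevents, nor the t-tests for the primary outcome, whose error runs the other way and is larger at low f.

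**What to change.** For every arm comparison, including the primary one at 24 months, state a model with a cluster random intercept and a fixed effect for the randomisation stratum. The stratum term should be included regardless of baseline balance, separately from the conditional rule for food security, education and SES. For LAZ, this model should replace the t-test as the primary analysis. That also deals with the ignored clustering.

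Union (12 levels) is the factor for which the article states the balance. Block (25 levels) follows the randomisation more closely, but the article does not say how clusters were grouped into blocks within a union, so any gain from the 13 further levels is undocumented. Either is acceptable if chosen in advance.

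The cost is one sentence in the analysis plan and 11 (union) or 24 (block) of 120 cluster-level degrees of freedom, leaving 109 or 96. If unions do not differ there is no gain, and that small loss is the only price.
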